### Sample size calculation

2.2

Currently, few studies have examined the effects of mobile phone-based microinterventions targeting valued living. To date, web interventions targeting valued living have reported effect sizes of *d* = 0.27 for hedonic well-being compared to no treatment [15]. Similarly, Bojanowska et al. [14] found *η*^2^ = 0.09 for hedonic well-being and *η*^2^ = 0.08 for eudaimonic well-being compared to a non-active control group. Therefore, the sample size for this study is determined based on effect sizes observed in prior studies (*f*^*2*^ ranging from 0.19 to 0.31). Specifically, we conducted a power analysis to detect an effect size of *f*^*2*^ = 0.25 for the within-between interaction in a repeated measures ANOVA with three groups (RWM, CWM, control) and three measurement points (baseline, post-intervention/two-week follow-up), with a significance level of 0.05 and statistical power of 0.80. The required sample size for the main analysis was 159 participants in total.

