**Fig. 2 fig2:**
[figure not shown]
Schedule of microinterventions. Abbreviations: FR: Friendly reminder

The 50th birthday party microintervention will be sent on the first day after downloading the app, and it will be sent only once with the following message: “It's time to start the journey! Listen to your first visualization”*.* When participants enter the app, this module will be named “Starting your journey!” and will remain available for the next 24 h. Throughout the day, participants will receive two reminders if the strategy has not been completed. The first reminder will be sent at 3:00 p.m. with the message: “Don't forget your first notification! It's really important to us that you complete it”. The second reminder will be sent at 9:00 p.m. with the message: “To stay in the study, please complete today's notification. We'd love to keep you on board!”

The 3-min wake-up microintervention will be sent daily in the morning during the 6 days following the initial microintervention, with the message: “Time for a quick exercise! It will disappear at 12:00 p.m.” When participants enter the app, this module will be named “Before starting your day!” and will be available from 6:00 a.m. to 12:00 p.m. Reminders will be sent at 9:00 a.m. and at 11:00 a.m. with the following messages, respectively: “Don't miss your morning check-in! It takes less than 5 min – Available until 12:00!” and “Don't forget about me! Morning notification disappears in 1 h”

The friendly reminder microintervention will be sent three times per day and will be available from 3:00 p.m. to 5:00 p.m., from 6:00 p.m. to 8:00 p.m., and from 9:00 p.m. to 11:00 p.m., on the same days as the morning notifications They will appear with the message: “Just 1 question”.

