### Statistical analysis

2.11

Data will be processed and analyzed with R 4.4.2 [66] or newer and the RStudio interface [67].

First, to test proximal and trajectory effects with and without photography, as well as the moderating role of quality of practice (Objectives 1.a, 1.b, 2, and 3), linear mixed-effects models will be fitted using the *lmerTest* package [68]. Separate models will be fitted for each proximal outcome within each microintervention as the dependent variables. For the 50th birthday party microintervention, participants from the RWM and CWM conditions will be pooled for the pre-post analysis, as the photography component in the CWM condition is introduced only after the post-microintervention EMA. Thus, time (pre- vs. post-microintervention), quality of practice, and their interaction will be entered as fixed-effect predictors. For values awareness, frequency of valued actions and awareness during valued actions, which require time and opportunity to occur or be noticed in daily life, change will be examined using the next available EMA assessment, collected the following day before the 3-min wake-up microintervention. Given that this assessment occurs after the photography task, models including condition will be conducted to examine potential RWM-CWM differences. For the 3-min wake-up microintervention, condition (RWM, CWM), time (pre- vs. post-microintervention), day (from 1 to 6), quality of practice, and their interactions will be entered as fixed-effect predictors. For the friendly reminder microintervention, condition (RWM, CWM, control), time (pre- vs. post-microintervention), day (from 1 to 6), quality of practice, and their interactions will be entered as fixed-effect predictors. Additionally, to examine the combined effect of the 3-min wake-up and friendly reminder microinterventions across the intervention period, linear mixed-effects models will be fitted using the variables assessed in the first EMA assessment of each day as dependent variables. This approach will allow us to examine whether values awareness, frequency of valued actions and awareness during valued actions change across repeated daily engagement with the intervention. Condition (RWM, CWM, control), day (from 1 to 6), and their interaction will be entered as fixed-effect predictors. Participant will be entered as a random-effect predictor in all models. Models will be estimated using restricted maximum likelihood (REML). Under the missing at random (MAR) assumption, all available data will be used, so participants with incomplete EMA data will still contribute to the analyses based on the observations they provide.

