
Second, to test the distal effects with and without photography on mental health and values-related outcomes (Objectives 1.c and 2), two-way mixed ANOVAs will be conducted with condition (RWM, CWM, control) as the between-subject factor and time (baseline, post-intervention, and two-week follow-up) as the within-subject factor. The inclusion of the MIA as a covariate will be performed if the assumptions for ANCOVA are met (objective 3).

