The proposed study also presents some limitations that should be considered. First, the English-language requirement may introduce selection bias and limit the generalisability of the findings, as students with lower English proficiency may be less likely to participate. Making the study materials available in both English and Dutch may broaden accessibility and enable future cross-cultural investigations. Moreover, participants may differ in motivation, expectations, or engagement depending on the pathway through which they enter the study, particularly when participation is linked to course credit. Although participants will be randomized and recruitment pathways will be recorded and examined across study arms, residual differences related to recruitment context may still influence adherence or outcome responses. Attrition is also expected in longitudinal experimental designs, especially in mobile phone-based interventions [[71], [72], [73]]. Difficulties in completing the tasks assigned during the intervention or a lack of understanding of the intervention rationale may increase this risk. To minimize the likelihood of drop-out, a predefined schedule with the study notifications will be sent to participants before the intervention period begins. A further limitation concerns the use of study-specific EMA items. Although these items were designed to assess theoretically relevant momentary constructs, their reliability and validity is yet to be established, and results involving these measures should be interpreted cautiously. Additionally, research has shown that internet-based interventions may have negative effects in some cases [74], including the worsening of existing symptoms or the emergence of new symptoms not directly addressed by the intervention. Values are also a sensitive topic and may evoke a range of emotional reactions. To provide support, a contact number and email address will be available throughout the study, particularly at the beginning of the intervention. This support will be available for both technical difficulties related to the app and emotional issues arising from the intervention. From the start of the study until the follow-up assessment, participants will be able to contact the research team by phone, text message, or email if they experience any of these difficulties. Previous research has shown that support in internet-based interventions is positively associated with treatment outcomes [75].

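### The mixed ANOVA for the distal outcomes implies a completers-only analysis and uses baseline inefficiently, while the plan's own all-available-data rule covers only the EMA models

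*Protocol article*

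**What the plan says.** Section 2.11 splits the analysis in two. Proximal and trajectory outcomes get linear mixed models fitted by REML in lmerTest, with this missing-data rule: "Under the missing at random (MAR) assumption, all available data will be used, so participants with incomplete EMA data will still contribute". Distal outcomes get a different method, introduced as one "to test the distal effects with and without photography on mental health and values-related outcomes (Objectives 1.c and 2", namely "two-way mixed ANOVAs will be conducted with condition (RWM, CWM, control) as the between-subject factor and time (baseline, post-intervention, and two-week follow-up". Baseline is therefore one of three levels of the within-subject factor. The only covariate considered is baseline mental imagery ability: "The inclusion of the MIA as a covariate will be performed if the assumptions for ANCOVA are met (objective 3". The baseline value of the outcome is not a covariate, and nothing is said about participants who lack T2 or T3.

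The limitations in the Discussion state: "Attrition is also expected in longitudinal experimental designs, especially in mobile phone-based interventions". Section 2.8 describes how T2 and T3 are pursued: an app notification, then an emailed survey link with a one-week window. It does not say how scores that stay missing are analysed. Section 2.2 bases the sample size of 159 on a repeated measures ANOVA, without an attrition allowance.

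**The concern.** A classical two-way mixed ANOVA works on participants with a value at every level of the within-subject factor. With three levels, one missing visit normally removes the person, including the scores that were collected. The plan recognises this problem for the EMA data, where it wants incomplete participants to contribute "so participants with incomplete EMA data will still contribute to the analyses based on the observations they provide", but it gives the distal outcomes no matching provision. The distal outcomes are the ones on which the sample size rests.

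Two things are at stake. First, observed data are discarded, and the comparison moves from everyone randomised to completers. If the chance of missing a visit depends on earlier scores, the completer comparison can be biased where a likelihood-based model under MAR is not. Second, a condition-by-time test that includes baseline as a time level compares changes from baseline. In a randomised trial the baseline-adjusted comparison estimates the same effect with smaller variance.

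**Working it through.** **Inputs.** From the article: three arms at 1:1:1 and N = 159 (sections 2.1 and 2.2), so 159/3 = 53 per arm; two-sided alpha 0.05; d = 0.27, the prior effect quoted in section 2.2. Assumptions, because the article gives no figures: correlation r between baseline and a later visit of 0.5 to 0.7, equal SD at all visits, and 20% or 30% of participants missing T2 or T3.

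**The plan's own figure.** Section 2.2 describes a within-between interaction with three groups and three time points. At an effect size of f = 0.25, that design gives N = 24 to 69, 99 to 102 or 195 to 198, depending on the convention for the noncentrality parameter and the correlation. It does not give 159. A one-way comparison of three groups (2 numerator df) with f = 0.25 does: power is 0.805 at N = 159. I use 159 below only to set 53 per arm.

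**Completers left.** At 20% missing, 159 × 0.80 = 127. At 30% missing, 159 × 0.70 = 111.

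**Can completers-only analysis bias the result?** Simulation with true effect 0.40 SD at T2 and T3 and r = 0.6 between all visits. T3 is missing more often after a poor T2 score in the active arm, and unrelated to scores in control. About 24% (active) and 27% (control) lack T3. The completers-only change contrast is 0.48 at T2 instead of 0.40, because observed T2 scores are thrown away. At T3 it is 0.40, with no bias under this equal-correlation set-up. Keeping all observed T2 scores removes the T2 bias. This shows the mechanism; it does not forecast this trial.

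**Efficiency of baseline handling.** In units of the outcome variance, per participant and at one visit:

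- change from baseline: 2(1 − r)
- baseline-adjusted: 1 − r²
- ratio: (1 − r²) / [2(1 − r)] = (1 + r)/2

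Pairwise power = Φ(d / √(2v/53) − 1.96), with v the variance above:

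| r | v, change | v, adjusted | ratio | power, change | power, adjusted |
|---|---|---|---|---|---|
| 0.5 | 1.00 | 0.75 | 0.75 | 0.28 | 0.36 |
| 0.6 | 0.80 | 0.64 | 0.80 | 0.34 | 0.41 |
| 0.7 | 0.60 | 0.51 | 0.85 | 0.43 | 0.49 |

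For r = 0.6: the change contrast has standard error √(0.80 × 2/53) = 0.174, so 0.27/0.174 = 1.55 and power is 0.34. The adjusted contrast has √(0.64 × 2/53) = 0.155, so 0.27/0.155 = 1.74 and power is 0.41.

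**The case against.** The best defence is that the article is condensed and pre-registered, and that missing-data handling and follow-up contrasts are commonly left to a fuller plan. The article never says that incomplete participants are excluded, and section 2.8 describes real efforts to retrieve T2 and T3. This defence limits the point but does not remove it: the article does name the distal method, and gives it no counterpart to the provision it makes for the EMA models.

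Several stronger readings are tempting, and the document does not support them:

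- *The plan states a complete-case analysis.* It does not; the named method implies one in standard use.
- *Baseline is wasted.* It enters through change over time. Under randomisation both approaches are unbiased, so the loss is one of efficiency.
- *Heavier tasks in the active arms will bias the completer comparison.* Unequal dropout rates by arm do not cause bias by themselves; missingness must also be related to outcomes. The article gives no dropout rates.
- *Participants who skip app tasks are withdrawn.* The day-1 reminder says "To stay in the study, please complete", but nothing in the article removes non-completers from T2 or T3.
- *Attrition lowers the planned power by a known amount.* Section 2.2 targets power with the words "with a significance level of 0.05 and statistical power of 0.80", but 159 does not follow from its stated design. At 111 completers, power for that design runs from 0.53 to above 0.99 by convention, so no single figure can be quoted.
- *The plan cannot separate Hypothesis 1 from Hypothesis 2.* The omnibus interaction alone does not separate them, but the article does not say that it alone decides either hypothesis. Contrasts may sit in a plan not shown.

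It is also fair to say that at d = 0.27 power is low either way; baseline adjustment improves it but does not rescue it.

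**Conclusion.** The point holds in limited form and should be fixed. The distal method implies a completers-only analysis in a trial that expects attrition, and it is inconsistent with the approach taken to EMA data in the same section. If 20% to 30% lack a visit, about 111 to 127 of 159 participants would remain. Bias is a risk that depends on missingness being related to earlier scores; it is not shown to occur. Separately, handling baseline as a time level leaves the contrast variance 18% to 33% higher than it need be (1/0.85 to 1/0.75). The correlation, the equal SDs and the dropout rates are assumptions.

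**What to change.** For each distal outcome, replace the mixed ANOVA with a linear mixed model fitted by REML in all randomised participants:

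- responses: the T2 and T3 scores
- fixed effects: condition, visit, condition × visit and the baseline score of that outcome
- participant random effect
- all available data, under MAR

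Alternatively, use a constrained-baseline model, with baseline as a response and a common mean across arms; this also keeps participants who have only baseline data. For the PHQ-9, Table 1 shows a screening score but none at T1, so the baseline covariate is the screening score.

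Report RWM minus control, CWM minus control, and CWM minus RWM at T2 and at T3 from this model.

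The cost is a few lines of code in lmerTest, which the plan already uses, and a dated update to the OSF registration. No new data are needed. Section 3 expected data collection to end in July 2025, so if results have already been seen, report both the registered and the revised analysis.

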### Data management and confidentiality

2.12

Given the sensitive nature of the mental health-related information collected in this study, strict confidentiality procedures consistent with the General Data Protection Regulation (GDPR) will be implemented. Participant data will be pseudonymized using unique participant codes, and personal identifying information will be stored separately from research data. Data collected through the TIIM app and online questionnaires will be transferred to and stored on protected institutional servers, with access restricted to authorized researchers. Data handling procedures will comply with institutional ethical requirements and applicable data protection regulations. In the CWM condition, photographs will be used solely as a personal reflective aid on participants’ own devices. The application will not include any function that allows participants to upload or share photographs with the research team. Therefore, no photographic data, including potentially identifiable visual information, will be collected, processed, stored, accessed, or analyzed by the researchers.

## Results

3

This study is ongoing and data collection is expected to be concluded in July 2025, with plans to publish the study results by November 2025.

## Discussion

4

This study presents the protocol for a three-arm randomized controlled trial designed to evaluate the effects of three mobile phone-based microinterventions targeting valued living on mental health and values-related outcomes in university students. In addition, the study will examine whether adding a photography component enhances intervention effects and whether quality of practice moderates proximal and trajectory effects.

This study may contribute to the literature at several levels. Theoretically, the study may inform the literature on positive psychological interventions (PPIs). Although values-focused work has been primarily developed within ACT, where values are understood as a key process for promoting psychological flexibility, it also aligns with positive psychology's emphasis on cultivating adaptive psychological resources that support well-being [69]. Following the model of sustainable mental health [9], valued living may also represent a complementary resource-oriented pathway for supporting adaptation, well-being, and mental health over time.

Conceptually, the study approaches valued living as a multidimensional process. This perspective extends traditional approaches that often conceptualize valued living as a unitary construct, allowing for a more fine-grained understanding of which values-related processes are most responsive to intervention and most strongly associated with well-being and mental health.

Regarding the intervention, the study evaluates values-based microinterventions as brief, targeted strategies designed to isolate and examine the specific effects of values work. This is relevant because values-related processes have often been embedded within broader multicomponent interventions, making it difficult to determine their unique contribution to mental health outcomes. The study also compares different values-oriented exercises, including strategies grounded in existing literature (i.e., 50th birthday party) and newly developed theory-informed exercises (i.e., 3-min wake-up and friendly reminder).

In terms of study design, the use of mobile technology enables these microinterventions to be delivered in participants’ daily lives, closer to their real-world experiences. EMIs may increase the accessibility and scalability of values-focused work while enabling the study of valued living as it unfolds in daily life. EMAs, in turn, allow the study to capture immediate changes in mental health and values-related processes, as well as their fluctuations within and across days.

Moreover, the study explores two potential pathways for strengthening the effects of values-focused work: participant-generated photography and quality of practice. Photography may strengthen values-focused work by making values more concrete, salient, and accessible, eliciting meaning-related affective states, and potentially improving adherence. Quality of practice, in turn, represents an initial step toward examining how the way values practices are implemented may influence intervention effects. This focus is particularly relevant because, although practice quality remains underexplored in PPIs, one of its components, mental imagery ability, has already been explored in gratitude and optimism exercises involving imagination-based strategies [70]. Examining these factors may help identify the conditions under which values-based microinterventions are most effective and inform the optimization of future values-based interventions.

The proposed study also presents some limitations that should be considered. First, the English-language requirement may introduce selection bias and limit the generalisability of the findings, as students with lower English proficiency may be less likely to participate. Making the study materials available in both English and Dutch may broaden accessibility and enable future cross-cultural investigations. Moreover, participants may differ in motivation, expectations, or engagement depending on the pathway through which they enter the study, particularly when participation is linked to course credit. Although participants will be randomized and recruitment pathways will be recorded and examined across study arms, residual differences related to recruitment context may still influence adherence or outcome responses. Attrition is also expected in longitudinal experimental designs, especially in mobile phone-based interventions [[71], [72], [73]]. Difficulties in completing the tasks assigned during the intervention or a lack of understanding of the intervention rationale may increase this risk. To minimize the likelihood of drop-out, a predefined schedule with the study notifications will be sent to participants before the intervention period begins. A further limitation concerns the use of study-specific EMA items. Although these items were designed to assess theoretically relevant momentary constructs, their reliability and validity is yet to be established, and results involving these measures should be interpreted cautiously. Additionally, research has shown that internet-based interventions may have negative effects in some cases [74], including the worsening of existing symptoms or the emergence of new symptoms not directly addressed by the intervention. Values are also a sensitive topic and may evoke a range of emotional reactions. To provide support, a contact number and email address will be available throughout the study, particularly at the beginning of the intervention. This support will be available for both technical difficulties related to the app and emotional issues arising from the intervention. From the start of the study until the follow-up assessment, participants will be able to contact the research team by phone, text message, or email if they experience any of these difficulties. Previous research has shown that support in internet-based interventions is positively associated with treatment outcomes [75].

Overall, this protocol outlines a theory-grounded and ecologically informed approach to examining valued living in daily life. By focusing on values-based microinterventions, proximal processes, and factors that may shape intervention effects, the study may offer useful directions for future research and applied work in mental health promotion.

